### Study setting

The ICH is a dedicated inpatient rehabilitation facility within Tan Tock Seng Hospital providing multidisciplinary rehabilitation for patients recovering from stroke, traumatic brain injury, orthopedic conditions, and other disabling conditions. The ward comprises single-bed cubicles, each equipped with a ceiling-mounted PreSAGE thermography camera connected to a centralized processing platform. Patients receive therapy five days per week during admission, which may include physiotherapy, occupational therapy, speech therapy, dietician consultation and/or psychological services depending on individual needs, and each therapy session lasts up to one hour. Clinical documentation uses the EPIC electronic medical record system. Based on Phase 1 data (*n* = 33), the median rehabilitation length of stay is 24 days (mean 27.3, SD,5 17.0, IQR, 15–35, range 4–70 days).

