### Phase 3: randomized multiple baseline evaluation (months 13–24)

#### Study design

The primary quantitative evaluation employs a randomized multiple baseline design across participants (28, 29, 32), in which each patient undergoes two phases during their admission:
**Phase A (Baseline Observation):** From admission, the PreSAGE system continuously monitors patient activity. Activity data are collected and processed but no feedback is provided to the patient or treating team. This observation-only period provides individualized baseline data for each patient, lasting 3 to 7 days depending on the randomly assigned onset point (see Randomization below), consistent with the A phase in SCED methodology (27, 31).**Phase B (Dashboard Intervention):** At the randomly assigned onset point, the patient-facing dashboard is activated on a bedside tablet and the clinician-facing dashboard becomes available to the treating team. Therapists set personalized activity goals, and patients receive continuous feedback on their progress. Thermographic monitoring continues throughout.The critical design feature is the randomized timing of the A-to-B transition. Each patient will be randomly assigned, using a computer-generated allocation sequence with concealed envelopes, to one of five onset points: post-admission day 3, 4, 5, 6, or 7. If the assigned onset day falls on a weekend, activation will be deferred to the next weekday to ensure research assistant availability and clinical team presence for goal-setting. This ensures that each patient has a minimum baseline observation period of 72 h (to establish a stable pre-intervention trend) while staggering the transition point across the sample in a manner consistent with the MBD framework (29, 32). Ten patients will be assigned to each of the five onset strata, yielding 50 patients total.

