### Sample size justification

Sample size estimation for the RMBD follows guidance from Kratochwill et al. (27) and Shadish et al. (41) on single-case experimental designs adapted for group-level analysis. The key considerations are: (a) the number of data points per phase per participant, and (b) the number of participants (replications).

With a median length of stay of 24 days (mean 27.3, SD 17.0) based on Phase 1 data, and randomized onset at days 3–7, each patient will contribute 3–7 baseline data points and a variable number of intervention data points. At the median stay, intervention points range from 17 to 21 days. Approximately 18% of Phase 1 patients had stays under 14 days; these patients will be included in the intention-to-treat analysis but contribute fewer post-onset observations. Shadish et al. (41) recommend a minimum of 3–5 data points per phase for SCED analyses. For the group-level multilevel analysis, we follow Moeyaert et al. (42), who demonstrated that 30 or more participants provide adequate power (>80%) for detecting medium effect sizes (d = 0.5) in multilevel models of SCED data with 20 time points per participant. Our planned sample of 50 patients with 21 daily data points each substantially exceeds this threshold.

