Additionally, Monte Carlo power simulations (2,000 replications) were conducted to evaluate the study's ability to detect intervention effects under the piecewise multilevel growth model. Data were generated assuming 50 participants (10 per onset stratum), a median of 24 daily observations each (based on Phase 1 empirical length of stay; IQR 15–35 days), a within-person residual standard deviation of 25 min, between-patient intercept standard deviation of 40 min, and within-person autocorrelation of 0.3. The study has greater than 80% power to detect an immediate level change of 10% in daily active time at dashboard onset (18 min; *α* = 0.05, two-sided), and greater than 99% power for a 15% level change (27 min, within-person d = 1.08). The study is primarily powered for the immediate level change parameter (*γ*₂₀); detection of the sustained slope change parameter (*γ*₃₀) would require larger per-day effects given the relatively short post-onset observation period. The sample of 50 provides adequate headroom for anticipated data attrition (early discharge, camera downtime) and planned subgroup analyses by functional level. We note that, while the sample is adequately powered for the primary immediate level-change parameter, the planned functional-level subgroup comparisons and the sustained slope-change parameter are powered to detect only larger effects given the shorter post-onset observation window; these analyses are therefore pre-specified as exploratory and hypothesis-generating rather than confirmatory.

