### Limitations

Several anticipated limitations should be acknowledged. First, the thermographic camera has a limited field of view covering only the bedside area, patient activities outside this zone (therapy gymnasium, bathroom visits, corridor ambulation) are not captured, potentially underestimating total daily activity. A check-in/check-out mechanism will partially mitigate this gap. Second, the single-site design may limit external generalizability, although the ICH serves a patient population typical of tertiary rehabilitation facilities in Singapore, and the qualitative component will explore transferability considerations. Third, the RMBD, while providing strong within-patient causal inference, relies on the assumption that the natural recovery trajectory is adequately modelled by the pre-intervention data points; patients with very short baseline periods (3 days) may have less stable baseline estimates (27, 41). Phase 1 data show substantial length of stay variability (SD 17.0, range 4–70 days), with 18.2% of patients staying fewer than 14 days; patients with short stays assigned to later onset strata will contribute limited post-onset data, though multilevel modelling accommodates unbalanced observations (27, 41). The inclusion of five onset strata and the multilevel modelling approach partially address this concern. Fourth, patients and staff cannot be blinded to dashboard activation, potentially introducing performance or Hawthorne effects; however, the objective, automated nature of the primary outcome measure minimizes this risk. Fifth, the system cannot detect small-motion exercises, and person identification within the camera's field of view remains a technical challenge when visitors or staff are present, although filtering algorithms are in development. Sixth, while the study substantially exceeds minimum SCED standards with 50 participants and five onset strata, the non-concurrent enrolment of participants (patients are recruited as they are admitted) means that the design functions as a non-concurrent MBD, which has been noted to have somewhat weaker internal validity than a fully concurrent design (31, 32); however, the sample size of 50 participants and randomization of onset timing substantially mitigate this concern. Seventh, the DREAMT intervention is multi-component, comprising continuous monitoring, a patient-facing dashboard, therapist-guided goal setting, and a clinician-facing dashboard. Because these elements are introduced together at dashboard activation, the design cannot isolate the independent contribution of any single component, and observed effects should be interpreted as those of the integrated intervention package; the qualitative process evaluation and the planned dose–response analyses of dashboard interaction will be used to generate, but not confirm, hypotheses about which components drive change. Finally, several stated advantages of the design and technology are anticipated rather than demonstrated, and the comparative and causal claims advanced in this protocol will require empirical confirmation once the study is complete.

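### Dashboard activation is never allowed on a weekend, but the primary model has no day-of-week term, so part of any weekend difference in measured activity can enter the level change γ20

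*Protocol article*

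**What the plan says.** Under Study design (Phase 3), each patient is randomised "to one of five onset points: post-admission day 3, 4, 5, 6, or 7", and "Ten patients will be assigned to each of the five onset strata, yielding 50 patients total". The same paragraph adds: "If the assigned onset day falls on a weekend, activation will be deferred to the next weekday". Under Study setting, "Patients receive therapy five days per week during admission". Under Limitations, "patient activities outside this zone (therapy gymnasium, bathroom visits, corridor ambulation) are not captured".

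Under Quantitative analysis, the Level 1 model is written out in full: an intercept, Day, Phase, Day_post and an AR(1) residual. It has no calendar term, and none of sensitivity analyses (a) to (e) adds one. Phase is defined as 0 in baseline and 1 once the dashboard is on, and Day_post counts days from activation. The closing sentence of that section, however, ties the intention-to-treat analysis to the day assigned at randomisation. The two days differ for every deferred patient.

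The Sample size justification says the trial is powered mainly for the immediate level change, γ20.

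**The concern.** The protocol's causal argument is that nothing else lines up with randomly varied onset days. The deferral rule breaks that argument for day of week. Assigned Saturdays, Sundays and Mondays all become Monday activations. The last baseline day is then a Sunday for every Monday activation, while the first dashboard day is never a weekend day.

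If on-camera active time has a weekly cycle, the weekend-to-weekday step coincides with the switch in Phase far more often than chance would produce. An AR(1) residual does not absorb a fixed weekly step. The parameter exposed is the one the trial is powered for. A quieter weekend would inflate γ20; a busier on-camera weekend would hide a real effect.

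**Working it through.** **Inputs from the protocol.** Onset days 3–7, 10 patients each, 50 in all; "a within-person residual standard deviation of 25 min, between-patient intercept standard deviation of 40 min, and within-person autocorrelation of 0.3"; two-sided α of 0.05; "the median rehabilitation length of stay is 24 days" (IQR 15–35). Day counting: "At the median stay, intervention points range from 17 to 21 days". Since 24 − 7 = 17 and 24 − 3 = 21, admission is day 0.

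**Assumptions, shown as ranges.** Admission weekday: even over seven days, or even over Monday–Friday. Weekend difference W (weekends W minutes lower): 9, 18 and 30 minutes. The protocol's 18 minutes is 10%, so its implied mean is 18/0.10 = 180 minutes, and these values are 5%, 10% and about 17% of it.

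**Step 1: the protocol's own power.** Generalised least squares for the stated model, with random intercept SD 40, residual SD 25 and AR(1) 0.3, gives SE(γ20) = 3.95 for 24 days each. Power = Φ(δ/SE − 1.96):
- δ = 18: Φ(4.56 − 1.96) = 99.5%.
- δ = 27: above 99.9%.

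Both stated lower bounds (above 80%, above 99%) hold. The SDs of the random slopes and random level change are not given. With an assumed level-change SD of 30, power is 87% and 99.6%.

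**Step 2: where activations fall.** Enumerating admission weekday × onset day:
- Seven-day admissions: 7 × 5 = 35 cells; 10 are deferred (29%) and 5 + 10 = 15 activate on Monday (43%).
- Monday–Friday admissions: 5 × 5 = 25 cells; 7 are deferred (28%) and 5 + 7 = 12 activate on Monday (48%).
- Weekend activations: none.

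**Step 3: leak into γ20, Phase coded by actual activation.** The leak is the GLS coefficient on Phase when the omitted mean is −W on weekends, divided by W. Type I error = Φ(b/SE − 1.96) + Φ(−b/SE − 1.96), with b = leak × W. The ranges cover stays of 15, 24 and 35 days.

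| Admissions | Leak | W = 9 | W = 18 | W = 30 |
|---|---|---|---|---|
| Seven-day | 0.31–0.37 | 11–13% | 32–39% | 69–80% |
| Monday–Friday | 0.46–0.50 | 19–20% | 59–60% | 95–96% |

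Worked cell (Monday–Friday, 24 days, W = 18): b = 0.479 × 18 = 8.6; b/SE = 8.6/3.90 = 2.21; Φ(2.21 − 1.96) = Φ(0.25) ≈ 60%.

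If the deferral is removed, the leak is 0 for seven-day admissions, so the rule itself creates it there. For Monday–Friday admissions about 0.17 remains at 24 days.

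The rejection rates depend on the unstated random-effect SDs. With a level-change SD of 30 and slope SDs of 2 (assumed), the leak stays at 0.34 and 0.50, but type I error at W = 30 falls to 43% and 73%.

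**Step 4: Phase coded by assigned day.** For 24 days the leak is 0 (seven-day) or about 0.17 (Monday–Friday). Undashboarded weekend days now count as Phase 1, however, and a true level change is recovered at only about 85% of its size.

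**Step 5: add a weekend indicator.** With actual-activation coding the leak becomes 0 and type I error returns to 5%. For 24 days SE moves from 3.82 to 3.86 (seven-day) and from 3.90 to 3.98 (Monday–Friday), that is 1% and 2%; the rise is at most 3.4%, for 15-day stays. Under assigned-day coding the indicator also removes the leak, but not the dilution.

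**The case against.** **The weekend difference is not documented.** This stands. The outcome is all non-lying time, including sitting in a chair. Therapy in the gymnasium is off camera, and a check-in/check-out mechanism is meant to close part of that gap. Neither the size nor the sign of a weekend difference can be derived. A reader might infer that the trial is bound to report a false positive, or that the rates at 30 minutes are what to expect. The protocol does not support that: 30 minutes is an illustration larger than the 27-minute effect in the power statement, and the bias may run the other way.

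**The intention-to-treat sentence may already settle the coding.** If Phase follows the assigned day, the leak largely disappears. This stands as a possible reading, but it conflicts with the definitions of Phase and Day_post, and it exchanges the bias for dilution. It shows that the protocol is unresolved, not that it is safe.

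**Sensitivity analysis (b), a one-day delay, would expose the artefact.** With actual-activation coding and 24 days, the delay cuts the leak to within ±0.06. It also recovers only about 26–29% of a true immediate effect. A fall in the estimate would therefore not tell the two apart, and the primary model would stay uncorrected.

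**The Monday share rests on assumed admission patterns.** This stands, which is why a range is given. That no activation falls on a weekend needs no such assumption.

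**Conclusion.** The point holds in conditional form. The deferral rule and the missing calendar term are both explicit in the protocol. With Phase coded by actual activation, as its definition reads, roughly 0.3 to 0.5 of any weekend difference enters γ20. An 18-minute difference would shift the estimate by about 0.3 × 18 = 5 to 0.5 × 18 = 9 minutes, against an 18-minute target effect. Even a 9-minute difference raises type I error to about 11–20% under the stated variances.

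These figures assume admission on day 0, one of the two admission patterns, and no large random level-change variance; a large one lowers the rejection rates but not the leak. Whether a weekend difference exists on camera, and in which direction, is unknown. Under assigned-day coding the concern becomes a smaller leak or none, plus dilution to about 85%.

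**What to change.** Before Phase 3 starts, add a weekend and public-holiday indicator, or day-of-week indicators, as a Level 1 fixed effect in the primary model and in the secondary models for daily series. The covariate is known from the calendar. The weekend indicator costs about 1–2% in standard error at 24 days and slightly more for short stays.

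Also state which day, assigned or actual activation, defines Phase and Day_post in the primary model, and make the variable definitions and the intention-to-treat sentence agree. If the assigned day is kept, say that the estimate is then diluted by the deferred days and allow for this in the power statement. Settling both points now avoids changing the primary model after the data have been seen.

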**Figure 1 F1:**
[figure not shown]
Schematic of the randomized multiple baseline design across participants. Each patient is continuously monitored from admission (baseline phase **A**, monitoring only) until a randomly assigned onset day (3–7 post-admission), at which the feedback dashboard is activated (intervention phase **B**). The staggered **A** → **B** transitions across the five onset strata, replicated across participants, allow improvements that coincide with dashboard activation to be distinguished from maturation, history, and regression to the mean. The daily total active time derived from continuous PreSAGE monitoring constitutes the primary outcome time series. Activity traces are illustrative.

### The DREAMT intervention

The DREAMT intervention is a multi-component digital health intervention comprising:
(1)*Continuous thermographic monitoring:* The PreSAGE system provides automated 24-hour activity data capture, processing, and classification using validated AI algorithms.(2)*Patient-facing feedback dashboard:* For functionally independent patients, the dashboard is accessible via a bedside tablet, displaying daily activity summaries (active time, sitting episodes, exercise counts), graphical progress toward personalized goals, and motivational prompts. For functionally dependent patients who may be unable to independently access the tablet, the dashboard functions primarily as a clinician-facing tool, with the care team using activity data to guide nursing engagement, turning schedules, and early mobilization decisions.(3)*Therapist-guided goal setting:* At the point of dashboard activation, therapists set initial personalized activity goals (e.g., daily minutes of sitting out of bed, exercise repetitions) based on the patient's baseline data and clinical status. Goals are reviewed and adjusted every 2–3 days using dashboard data.(4)*Clinician-facing dashboard:* Providing the care team with activity trend data, nursing engagement metrics, sleep indicators, and patient progress visualizations to support clinical decision-making and care coordination.

### Outcome measures

The primary outcome is daily total active time (minutes per day), defined as time spent in non-lying postures (sitting on bed edge, sitting in chair, standing, walking, exercising) as continuously measured by the PreSAGE system. This outcome is aggregated daily and analysed as a within-patient time series. The validity of this AI-derived measure will be established against clinician-rated ground truth during Phase 2 validation (accuracy, precision, recall, F1, and AUROC), and only activity states meeting a pre-specified per-class reliability threshold (F1 ≥ 0.80) will contribute to the primary metric; states with lower reliability (for example, small-motion exercises) are reported descriptively and excluded from the primary outcome. Because individual rehabilitation prescriptions are heterogeneous and patient-specific, personalised therapist-set goals are evaluated as a patient-referenced secondary outcome rather than folded into the primary measure, which is defined identically for all participants to preserve comparability across the cohort.

Secondary quantitative outcomes include: (a) daily number and duration of sitting-out-of-bed episodes; (b) daily exercise frequency and duration, disaggregated by upper and lower limb exercises; (c) daily proportion of prescribed exercises completed (exercise compliance rate); (d) number of goals set and achieved per day; (e) dashboard utilization (daily interaction count and duration); (f) FIM score change from admission to discharge; (g) FAC score change; (h) MBI score change; (i) length of stay (days); (j) discharge destination (home, community hospital, skilled nursing facility); (k) incidence of complications (pressure injuries, deep vein thrombosis, falls, hospital-acquired infections); (l) nursing engagement frequency and duration across activity types (wound dressing, diaper change, dressing, intravenous management, patient calls, nasogastric tube feeding, assisted feeding, medication administration, vital signs monitoring), recorded as episode count and cumulative minutes per day; (m) time to first sit-out-of-bed episode post-admission; (n) complication rates (pressure injuries, deep vein thrombosis) analyzed by functional level subgroup.

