### Randomization and blinding

Randomization of dashboard onset timing will be performed using a computer-generated random number sequence, consistent with recommendations for randomized SCEDs (27, 28). Allocation will be concealed using sequentially numbered, opaque, sealed envelopes prepared by a statistician not involved in recruitment. Patients will be stratified by primary diagnosis (stroke vs. non-stroke) and baseline functional level [dependent [FIM motor score ≤58] vs. independent [FIM motor score >58]] to ensure balanced representation across onset strata. Neither patients nor clinical staff can be blinded to dashboard activation, as the intervention involves an active visual feedback display. However, the primary outcome (daily active time) is measured objectively and continuously by the PreSAGE system, eliminating observer bias in outcome ascertainment. The statistician conducting the primary analysis will be blinded to onset stratum assignments.

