### Qualitative component: semi-structured interviews

A qualitative process evaluation will be conducted following Phase 3 data collection, consistent with the explanatory sequential design (34). The qualitative component follows the Medical Research Council framework for process evaluation of complex interventions (35) and will explore: (a) participant experiences with the monitoring system and dashboard, (b) perceived mechanisms of effect (or lack thereof), (c) barriers and facilitators to engagement, (d) privacy perceptions, and (e) contextual factors influencing implementation.

Purposive sampling will recruit participants representing diverse perspectives:
**Patients (*n*** **=** **10–15):** Sampled for maximum variation in age, diagnosis, functional level, and dashboard engagement level (high, moderate, and low users as defined by interaction frequency terciles). Interviews will be conducted within 48 h prior to planned discharge.**Ward sisters (*n*** **=** **2–3):** Senior nursing staff responsible for resource planning and dashboard-informed workflow decisions.**Clinicians (*n*** **=** **4–6):** Including therapists (physiotherapists and occupational therapists) and physicians involved in dashboard-informed goal setting and clinical decision-making.Topic guides will be developed based on the study objectives, piloted with two participants from each group, and iteratively refined. Interviews will be audio-recorded with consent, transcribed verbatim, and de-identified. Analysis will use reflexive thematic analysis (43) following Braun and Clarke's six-phase approach: familiarization with the data, generating initial codes, constructing themes, reviewing themes, defining and naming themes, and writing up. Two researchers will independently code 25% of transcripts; discrepancies will be resolved through discussion to enhance analytical rigor. Thematic saturation will be assessed using an information power framework (44), considering the study's specific aims, sample specificity, and theoretical positioning. NVivo (Lumivero) will be used for data management.

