Secondary analyses for clinical outcomes (FIM, FAC, MBI, length of stay, discharge destination, complications) will use generalized linear models adjusted for baseline characteristics. Dashboard utilization patterns will be explored using descriptive statistics and latent class analysis to identify distinct engagement profiles. Subgroup analyses will compare intervention effects between functionally dependent and independent patients, with the hypothesis that dependent patients may show primary improvements in clinician-mediated outcomes (nursing engagement frequency, time to first sit-out, complication rates) while independent patients may show primary improvements in self-directed activity outcomes (daily active time, exercise compliance, dashboard utilization). The dose-response relationship between dashboard interaction frequency and activity changes will be examined using the interaction count as a time-varying covariate in the multilevel model.

All quantitative analyses will be conducted using R (R Foundation for Statistical Computing, Vienna, Austria) with the “lme4”, “nlme”, 'SingleCaseES', and “brms” packages.

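### Dashboard utilisation is one interaction count for all patients, not conditioned on functional level, so a low count can reflect functional level rather than low engagement

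*Protocol article*

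**What the plan says.** **The measure.** Outcome measures lists "e) dashboard utilization (daily interaction count and duration" among the secondary outcomes. It sets no limit by functional level and does not say whether patient use, staff use or both are counted.

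**Who uses the dashboard.** The DREAMT intervention section splits by functional level: "For functionally independent patients, the dashboard is accessible via a bedside tablet", whereas "For functionally dependent patients who may be unable to independently access the tablet, the dashboard functions primarily as a clinician-facing tool". The Phase 3 Study design section makes no such split; at onset "the patient-facing dashboard is activated on a bedside tablet and the clinician-facing dashboard becomes available to the treating team".

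**Functional level.** Randomization and blinding stratifies by "baseline functional level [dependent [FIM motor score ≤58] vs. independent [FIM motor score >58", so dependent patients are a planned part of the sample. Their expected share is not stated.

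**Uses of the count.**
- The qualitative component defines users as "high, moderate, and low users as defined by interaction frequency terciles".
- Quantitative analysis plans "latent class analysis to identify distinct engagement profiles".
- The same section enters the interaction count as a time-varying covariate to study dose-response.

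None of the three is said to be stratified by, or adjusted for, functional level.

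**The concern.** Under the intervention section, a dependent patient may have few tablet interactions because someone else reads the dashboard on that patient's behalf. Under the outcome definition, the same patient is scored as a low user. If staff interactions are counted as well, the number mixes two different behaviours. In either case the count does not mean the same thing in the two functional groups.

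The consequence lies in interpretation. Interviewees chosen as low users could be largely patients who were not the main intended tablet users. A low-engagement class could partly reproduce the FIM motor cut. The joint display asks whether patients reporting usability barriers interact less and gain less activity; that comparison would be partly one of functional levels. The interview selection cannot be repeated, because patient interviews take place within 48 hours before planned discharge. If the logs do not separate patient from staff use, no later analysis can recover the split.

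**Working it through.** The plan states no figure on this point, so there is none to reproduce. The check asks how far pooled terciles separate patients by functional level, and how far the dose-response coefficient is affected.

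**Inputs from the article:** 50 patients; median stay 24 days; onset on days 3–7; residual SD 25 min; intercept SD 40 min; autocorrelation 0.3.

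**Assumed, because the article gives neither:** the dependent share (20–70%), and the dependent patients' interaction rate relative to independent patients (2% to 100%). Also assumed: a mean of 4 interactions per day in independent patients, with gamma-distributed variation between patients (shape 1.5) and Poisson daily counts.

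**Step 1: limits by arithmetic.** A tercile holds 50/3 = 16.7, about 17 patients. If every dependent patient ranks lowest:
- share 20%: 10/17 = 59% of the low tercile
- share 30%: 15/17 = 88%
- share 34% or more: 17/17 = 100%, since 17/50 = 34%

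**Step 2: tercile composition when the rate varies** (1,500 simulated samples per cell). Percentage of the low tercile who are dependent:

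| Dependent share | Rate 2% | 10% | 30% | 50% | 100% |
|---|---|---|---|---|---|
| 20% | 59 | 56 | 43 | 33 | 20 |
| 30% | 87 | 77 | 58 | 46 | 30 |
| 40% | 97 | 88 | 70 | 58 | 40 |
| 50% | 99 | 93 | 78 | 67 | 50 |
| 60% | 99 | 96 | 85 | 76 | 60 |
| 70% | 99 | 97 | 90 | 83 | 70 |

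The 2% column agrees with the limits in step 1. For shares of 30–50%, functional level explains 53–80% of the variance in log interaction rate at relative rates of 2–10%, 25–28% at 30%, and 11–13% at 50%. At relative rates of 2–10% dependent patients make up 0–1% of the high tercile. At equal rates the low tercile has the same dependent share as the whole sample.

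**Step 3: dose-response.** Data were simulated with no true effect of the count (60 runs per setting, 24 days per patient, SD of the activation effect 15 min). The fitted model had random intercepts and random phase effects; it left out random slopes and the AR(1) residual.

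| Dependent share, relative rate | Activation effect, independent / dependent (min) | Raw count: mean coefficient (share with p < 0.05) | With functional level by phase | With between-patient mean |
|---|---|---|---|---|
| 50%, 10% | 30 / 5 | +0.38 (0.08) | −0.01 (0.05) | −0.06 (0.05) |
| 30%, 10% | 30 / 5 | +0.32 (0.12) | +0.05 (0.02) | +0.09 (0.03) |
| 50%, 2% | 40 / 0 | +0.51 (0.17) | −0.03 (0.07) | −0.08 (0.05) |
| 50%, 10% | 18 / 18 | +0.16 (0.03) | +0.08 (0.03) | +0.05 (0.03) |

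Coefficients are minutes per interaction. At 4 interactions per day, +0.32 to +0.51 amounts to about 4 × 0.32 = 1.3 to 4 × 0.51 = 2.0 min, against the 18 min on which the study is powered. With 60 runs, the Monte Carlo standard error of a 0.05 rate is √(0.05 × 0.95/60) = 0.028, so 0.08 cannot be told apart from nominal. The higher rates appear only when the activation effect is assumed to differ strongly between the groups.

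**The case against.** **The text is hedged.** A reader might infer that dependent patients never use the tablet and so have structural zeros. The documents do not support this. They say that such patients may be unable to use it without help and that the dashboard is mainly, not only, for clinicians. Assisted use is possible, and the Study design section activates the tablet without regard to function. This stands, and it is why the relative rate has to be varied. It does not remove the problem, because the article nowhere says that the two groups' counts are comparable.

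**Staff use may count.** If clinician-view interactions are included, dependent patients need not be low users. This is true, but the count would then not measure patient engagement.

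**The authors foresaw the difference.** They plan comparisons by functional level and expect utilisation gains mainly in independent patients. Interviews also vary other characteristics: "Sampled for maximum variation in age, diagnosis, functional level, and dashboard engagement level". The Limitations section treats the dose-response as hypothesis-generating. These points reduce the harm. They leave the definition of a low user unchanged, and sampling on both attributes is difficult if low use and dependence nearly coincide.

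**It is detail for a fuller document.** Rules for scoring zeros or for class-model covariates can be left there, and their absence is no fault. The article itself, however, fixes a single count and tercile-based user groups, and these conflict with its own description of who uses the tablet.

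**Low use through inability is itself a barrier.** That is fair for the joint display, and it argues for keeping dependent patients in the interview sample.

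**Conclusion.** The point holds in limited form. One interaction count serves all patients although the article gives the dashboard a different main user in each functional group, and its three uses are not conditioned on functional level. A low count can therefore reflect functional level rather than low engagement.

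For terciles, the size runs from no distortion at equal rates, through 46–67% of the low tercile at half the rate, to 77–99% at 2–10% of the rate, each for a dependent share of 30–50%. At a 20% share dependent patients fill at most 59%. Both inputs are assumptions. The latent classes were not simulated; the variance explained in step 2 shows how closely they could follow functional level.

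A reader might go further and conclude that the engagement measures, including the dose-response, mostly measure functional level. The documents do not support that in general. For terciles and classes it is true only if dependent patients are about 30% or more of the sample and rarely use the tablet. The dose-response draws mainly on day-to-day variation within patients, and its simulated bias was modest.

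Only secondary and exploratory analyses and the mixed-methods interpretation are affected. The primary outcome, primary test and sample size are not. The change is worth making before Phase 3, because it depends on what is logged.

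**What to change.** 1. Log patient-view and clinician-view interactions separately, and do not pool them. State which of them the utilisation outcome uses.
2. Record at activation whether the patient-facing tablet is in use for that patient. The Results section plans printed daily summaries until tablets are integrated; a patient given print alone would also have no tablet interactions.
3. Reconcile the Study design and DREAMT intervention sections on how the patient-facing dashboard applies to each functional group.
4. Form the interview terciles within functional level. The dependent share is then equal across terciles by construction, and dependent patients stay in the interview sample. Restricting the terciles to tablet users would remove them.
5. Report utilisation and engagement classes by functional level, or among tablet users.
6. In the dose-response model, separate within- from between-patient counts, or include functional level and its interaction with phase. In step 3 either change brought the spurious coefficient to between −0.08 and +0.09.

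**Cost.** One recorded flag, one logging requirement and some wording. Groups become smaller: at an assumed 30% dependent share, terciles within level hold 15/3 = 5 dependent and 35/3 ≈ 12 independent patients. If most dependent patients have counts near zero, ranking within that group will carry little information, and the report should say so.
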